### GBS accessibility and exposure dataset

There is no clear consensus in the existing literature on the most appropriate measures of GBS access and/or exposure.^42^ Using the aforementioned environment datasets, this project will collate a set of measures using criteria including longitudinal consistency, spatial resolution and evidence for associations with mental health and SWB outcomes. We will create residential-level exposure measures by modelling the ambient home environment, that is, the GBS immediately surrounding their home and what they see out of their window. This metric will include measures such as greenness (NDVI), urban trees and garden size. The access measures will represent people’s potential to visit GBS in their locality. We will adapt a previous methodology that modelled ‘change in alcohol outlet density and alcohol-related harm to population health’ (CHALICE).^60^ The distance decay for this accessibility model will be updated to emulate how people engage with GBS as opposed to alcohol outlets. People will behave differently in accessing GBS, compared with how they may access alcohol outlets. For example, people may be prepared to walk or drive further to access some green blue spaces compared with alcohol outlets.^61^ Our modelling will consider differential associations for key subgroups (eg, deprived populations) thereby minimising risks that recommendations could increase inequalities. We will create a number of accessibility and exposure measures, allowing planners to consider the configuration (size, function, quality) of the most beneficial mix of spaces. We will also measure, for each adult, change in GBS access and exposure for the study period. Again, we will build on the CHALICE study^62^ that measured change in alcohol outlet density by calculating change in density between the current and previous quarter and also the change between each quarter and baseline.

The longitudinal, household-level, GBS accessibility and exposure dataset will be imported into the SAIL databank and linked with health datasets that are held within the SAIL Databank. Household identifiers (Unique Property Reference Numbers, UPRNs) will be used to distinguish each household in the GIS and will have attached to each a GBS accessibility and exposure index (see figure 3). Household identifiers will be replaced with a Residential Anonymised Linking Field within SAIL.^63^

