## Statistical analysis

### Outcome variables

#### WP1 and 2: primary outcome - CMD

Change in counts of CMD treatments for adults identified as CMD cases within the corresponding time periods for the 70% of adults in Wales for whom we have GP data records in SAIL (1.7M adults). Prevalence algorithms,^65 66^ detect cases of CMD (anxiety and depression) from routinely collected GP data. We will use the algorithm that incorporates: an historical diagnosis and currently treated, with current diagnosis whether treated or untreated, to identify CMD cases. For each adult, and for the time periods (quarters) identified as a CMD case, treatments will be counted per day and aggregated into quarterly counts. Figure 4 shows a conceptual model of exposure variable (GBS access and exposure) and primary outcome variable (CMD treatments).

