### Analysis plan

We will provide descriptive statistics of GBS access and exposure and changes in GBS access and exposure by household, Lower Layer Super Output Area (LSOA), deprivation quintiles using Welsh Index of Multiple Deprivation (WIMD) and population characteristics. NSW data will have descriptive statistics of each of the survey questions we will use (number of visits, labour market status, etc).

Across both WPs, we have outcomes of two distinct types: continuous (SWB) and counts (CMD treatments and GP event days). We intend to analyse the continuous outcome using a linear model. Poisson models will be used to analyse the longitudinal count data.

Our data are hierarchical in nature: WP1: three-level data: LSOA/Individual/Time (Quarter); WP2: two-level data: LSOA/Individual. Accordingly, we will adopt a multilevel modelling approach. We will generalise the standard linear and Poisson models to handle two or three levels of variation, as appropriate. The resulting two-level and three-level models will allow us to estimate the extent to which variation at each level may be explained by confounding variables (see table 2). Having controlled for confounders, we will proceed to add access and exposure variables to our models, thereby allowing us to test for the significance of the access and exposure variables in the presence of the confounders. Inclusion of these variables in the above models will permit us to estimate their direct effects on our outcomes. Having included the main effects of both confounders and access and exposure variables, we will proceed to test for the significance of selected pairwise interactions of interest, as shown in table 2.

**Table 2 T2:** Analysis summary (P: primary; S: secondary)

WP	Outcomes (type)	Exposures	Confounders	Interactions of interest
1	P: CMD (count)	P: Access and exposure to GBS.	LSOA level: Quintile of deprivation (WIMD). Category of urban/rural settlement type (ONS classification).	Change in access and exposure to GBS by deprivation.
	S: GP event days (count)	S: Time of move(s).	Individual level (SAIL): gender, age, comorbidities.	Change in access and exposure to GBS by time of move(s).
2	P2: SWB (continuous)	P2: Access and exposure to GBS.	LSOA level: as per WP1.	Exact number of visits by individual level deprivation.

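### The inequality safeguard rests on a Poisson deprivation interaction, which tests equal rate ratios and does not by itself show whether the absolute gap widens or narrows

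*Protocol article*

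**What the plan says.** In the section on the GBS accessibility and exposure dataset, the article makes a claim about what the modelling achieves: "Our modelling will consider differential associations for key subgroups (eg, deprived populations) thereby minimising risks that recommendations could increase inequalities".

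The Analysis plan gives the method. For the counts, "Poisson models will be used to analyse the longitudinal count data". The hierarchy is handled by extension: "We will generalise the standard linear and Poisson models to handle two or three levels of variation, as appropriate". After the main effects, "we will proceed to test for the significance of selected pairwise interactions of interest, as shown in table 2". The deprivation entry for WP1 in Table 2 is "Change in access and exposure to GBS by deprivation", and deprivation is entered as the area-level WIMD quintile.

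The primary outcome is defined as "Change in counts of CMD treatments for adults identified as CMD cases within the corresponding time periods", aggregated to quarterly counts.

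The Analysis plan also promises descriptive statistics by WIMD quintile. These describe GBS access and exposure and their changes, not the effect of GBS on outcomes.

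**The concern.** The safeguard is a claim about inequalities, and an inequality in treatment rates can be measured as a ratio or as a difference. A product term in a log-link Poisson model addresses only the ratio. When baseline rates differ between deprivation groups and GBS has an effect, equal rate ratios and equal rate differences cannot both hold, so an answer on one scale does not give the answer on the other.

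Two misreadings are at stake. A significant positive product term could be taken to mean that improving GBS would widen inequality, when the absolute gap in treatments is unchanged or narrower. A null or negative term could be taken as reassurance when a loss of GBS is widening the absolute gap. Both matter because the article directs its results to planners and policy-makers, and because the study concerns changes in GBS in either direction.

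**Working it through.** **Inputs.** From the documents: Poisson model, product term of GBS change by deprivation, significance test. Not in the documents: the link function, CMD treatment rates by deprivation, and effect sizes. The log link is taken as the standard one; all rates and rate ratios (RR) below are assumptions. There is no figure in the plan to reproduce.

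**What the product term tests.** Let X be a GBS change and D deprivation (most versus least), with log μ = a + bX + cD + dXD. Then exp(d) = RR_D / RR_L, so d = 0 means equal rate ratios. With baseline rates r_D and r_L, the absolute gap changes by r_D(RR_D − 1) − r_L(RR_L − 1), which also depends on the baseline rates.

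**Worked case, GBS gain.** With r_L = 1.0, r_D = 2.0, RR_L = 0.90 and RR_D = 0.92:
- exp(d) = 0.92 / 0.90 = 1.022, which reads as less relative benefit in the deprived group.
- Ratio between groups: 2.00 → 1.84 / 0.90 = 2.044 (wider).
- Gap: 1.00 → 1.84 − 0.90 = 0.94 (narrower).
- Treatments saved per 1000 person-quarters: 100 in the least deprived, 160 in the most deprived.

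**Worked case, GBS loss.** Same rates, RR_L = 1.10 and RR_D = 1.08:
- Ratio: 2.00 → 2.16 / 1.10 = 1.964 (narrower).
- Gap: 1.00 → 2.16 − 1.10 = 1.06 (wider).

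**Dependence on the baseline ratio** k = r_D / r_L, with r_L = 1.0 and RRs of 0.90 and 0.92:

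| k | Ratio between groups | Absolute gap |
|---|---|---|
| 2 | 2.000 → 2.044 | 1.00 → 0.94 |
| 1.5 | 1.500 → 1.533 | 0.50 → 0.48 |
| 1.25 | 1.250 → 1.278 | 0.25 → 0.25 |
| 1.1 | 1.100 → 1.124 | 0.100 → 0.112 |

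At k = 1.1 the two scales agree. In general, for k > 1 and both RRs below 1, the signs conflict exactly when RR_L < RR_D < 1 − (1 − RR_L)/k. With RR_L = 0.90 the upper limit is 0.909 (k = 1.1), 0.920 (1.25), 0.933 (1.5), 0.950 (2) and 0.967 (3). The band closes as k approaches 1.

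**Direction.** In that setting (k > 1, both RRs below 1), if RR_D ≤ RR_L then k(1 − RR_D) > 1 − RR_L, so the gap must narrow. Relative narrowing with absolute widening is therefore impossible there; it needs RRs above 1, as in the loss case.

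**Could the tests differ in practice?** One simulated data set (200,000 independent person-quarters, true rates 1.0 and 2.0, RRs 0.90 and 0.92) gave d = 0.0236, SE 0.0079, p = 0.003, while the observed gap fell from 1.004 to 0.949.

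Closed-form power, with four cells of 50,000 and baseline rates of 0.30 and 0.60:
- Equal absolute benefit of 0.03 (RRs 0.90 and 0.95): log interaction ln(0.95/0.90) = 0.0541. SE = √[(1/0.30 + 1/0.27 + 1/0.60 + 1/0.57)/50,000] = 0.0145, so power is 96%, although the gap is unchanged.
- Equal RR of 0.90: difference contrast 0.06 − 0.03 = 0.03. SE = √[(0.30 + 0.27 + 0.60 + 0.54)/50,000] = 0.0058, so power is above 99%, although the log interaction is exactly zero.

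**The case against.** The strongest reply is that the article never says the inequality judgement will rest on the Poisson product term. The claim stands in one section and the interaction test in another, and scale and post-estimation contrasts are normally left to an analysis plan. This stands in part: a reader might infer that absolute results will never be reported, and the documents do not support that. What remains is that the article asserts a safeguard, and the only WP1 analysis of differential association it states does not settle the question. The descriptive tables by quintile do not fill the gap, because they do not concern outcomes.

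A second reply is that relative inequality is a legitimate measure. This stands. A reader might infer that the additive scale is the right one, but the article does not define inequality as absolute. In the equal-absolute-benefit case above, the ratio does widen, from 2.00 to 0.57/0.27 = 2.11.

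Third, the outcome counts treatments among identified cases. A rate difference on that outcome is not the gap in CMD burden in the population, because it leaves out how many people are cases. This stands and limits the wording of any conclusion.

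Fourth, for a beneficial GBS gain with higher rates in deprived groups, sign conflicts are false alarms rather than concealed harm. This also stands, for that setting only.

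Finally, a reader might see WP1 and WP2 as inconsistent, since SWB is analysed on the additive scale ("We intend to analyse the continuous outcome using a linear model"). That is weak: the interactions listed for WP2 concern number of visits, not GBS change by deprivation, so they ask different questions whatever the scale.

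**Conclusion.** The point holds as a mismatch between a stated safeguard and the one WP1 test offered for it. Under a log link, the product term answers whether rate ratios are equal. If baseline treatment rates differ by deprivation, it can give the opposite sign to the change in the absolute gap, as in the two worked cases (gap 1.00 to 0.94 with a wider ratio; 1.00 to 1.06 with a narrower one).

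The size rests on assumed rates, rate ratios and link. The documents give neither the size nor the direction of the baseline difference, and near a baseline ratio of 1 the conflict almost disappears. The power figures assume independent observations and a simple two-by-two layout.

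A reader might infer that the two scales would almost surely diverge at the planned size of 1.7 million adults. The documents do not support this: the number of case-quarters is not given, and clustering and overdispersion are not allowed for here. Nor do they support saying that the plan would systematically hide widening inequalities. The repair is worth making because it is cheap and can change the inequality conclusion.

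**What to change.** Keep the Poisson interaction and state that it is on the rate-ratio scale. For each WP1 interaction with deprivation, also report from the same fitted model:
- standardised quarterly rates by WIMD quintile at a lower and a higher level of GBS, the levels fixed in advance;
- the rate difference within each quintile;
- the contrast of rate differences between the most and least deprived quintiles, with 95% CI.

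Rest statements about inequality on both scales and not on the product-term p-value alone. Where the scales disagree, say so. Word the conclusions for the primary outcome as treatment counts among CMD cases, not as population CMD burden.

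The cost is post-estimation of models already planned and a sentence or two in the plan. The downside is a second set of interaction results to present and explain.

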### Health datasets

#### Welsh Longitudinal General Practice

The Welsh Longitudinal General Practice (WLGP) dataset contains individual-level health data including Read codes^64^ for all diagnoses, symptoms and treatments recorded by a GP and we will extract outcome data for each person from 2008 to 2018.

### Welsh Demographic Service

The Welsh Demographic Service (WDS) dataset contains addresses for all individuals who register with a GP. Dates for each address record update are recorded, thereby providing durations of residency for multiple homes and the ability to link to local environment indices at each time point. This dataset holds demographic data including age and gender. These data will be used to create population subgroups based on age, gender and location for each period. The WDS contains historical patient provided address information linked anonymously at the individual level (the ALF) which is the primary key variable for record linkage.^52 53^

### National Survey for Wales

The NSW is a cross-sectional, representative sample of adult participants across Wales. Participants answer questions on public services such as education, transport, leisure activities, and self-reported health and well-being. They also report information on visits to GBS, such as visit frequency and activities undertaken during visits.

Figure 3 shows how GBS accessibility indices will be generated and linked with routinely collected health and survey data held within the SAIL Databank. Table 1 shows the data sources and variables that we plan to derive from the routinely collected health data, survey dataset, and population register that are available in the SAIL Databank.

**Table 1 T1:** Data sources for outcome and accessibility/exposure variables to be used in statistical analysis for years 2008–2018

Dataset name	Data source	Derived variables	Coverage	Work package (WP)
GBS accessibility and exposure dataset.	Local authorities, ordnance survey, satellite data sources.	Typology to be developed. The dataset will include GBS such as parks, woodland, sports facilities, trees in residential areas.	Wales.	WP1 and WP2
Welsh Longitudinal General Practice dataset (core SAIL dataset).	Primary care records recorded by GP.	CMDs such as anxiety and depression (see outcome variable section for details).	70% of practices in Wales provide data to SAIL.	WP1 and WP2
Welsh Demographic Service dataset (core SAIL dataset).	NHS Wales Informatics Service.	Age, gender, week of birth, multiple move in and out of home dates.	Total population of Wales who are registered with a GP, a free to use service in the UK.	WP1 and WP2
National Survey for Wales (restricted SAIL dataset).	Welsh Government.	Subjective well-being, self-reported visits to GBS.	Cross-sectional, representative sample approximately 12 000 participants per year.	WP2

GBS, green-blue spaces; GP, general practitioner; CMDs, common mental health disorders; SAIL, Secure Anonymised Information Linkage.

## Statistical analysis

### Outcome variables

#### WP1 and 2: primary outcome - CMD

Change in counts of CMD treatments for adults identified as CMD cases within the corresponding time periods for the 70% of adults in Wales for whom we have GP data records in SAIL (1.7M adults). Prevalence algorithms,^65 66^ detect cases of CMD (anxiety and depression) from routinely collected GP data. We will use the algorithm that incorporates: an historical diagnosis and currently treated, with current diagnosis whether treated or untreated, to identify CMD cases. For each adult, and for the time periods (quarters) identified as a CMD case, treatments will be counted per day and aggregated into quarterly counts. Figure 4 shows a conceptual model of exposure variable (GBS access and exposure) and primary outcome variable (CMD treatments).

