### Objectives

#### WP1

Create a longitudinal dataset of GBS in Wales using UK Ordnance Survey (OS), local authority and remotely sensed satellite data.Create longitudinal, residential GBS accessibility indices for all homes in Wales using the longitudinal GBS dataset in a Geographic Information System (GIS).Create an 11-year dynamic cohort of individual-level longitudinal residential GBS accessibility indices to answer the research question(s): ‘Do people with different GBS access through time have different associated risks of having a CMD?’ and ‘Is the association between changes in access and exposure to GBS and CMD modified by multiple sociophysical variables, migration and socioeconomic disadvantage?’

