## Methods and analysis

### Design

The GBS project is a retrospective and controlled, population-wide study. We will evaluate the association between changes in access and exposure to GBS, on the risk of CMD (WP1) and SWB (WP2). This could be either at environment level (eg, a change in the GBS itself) or person level (eg, moving home, better access to transport). WP1 will use longitudinal data to examine variability in time and space of access and exposure to GBS and examine whether this could be due to planning and environmental policies. WP2 will use cross-sectional data to investigate whether visits to GBS improve SWB.

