Another aim of the study is to create novel GBS accessibility indices to use network routes from a variety of sources, and access points, to model how people may access GBS. The way that studies measure access to GBS is methodologically diverse and there is no general consensus on which is the best measure to use. Our measures will be informed by theories and findings in the literature. To complement this, we will ensure we involve members of the public in our research. The overarching aim of our longitudinal study is to identify causal mechanisms to determine whether a positive change in access and exposure to GBS lowers the risk of CMD.

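### The WP1 primary outcome, a treatment count in adults and quarters already classed as CMD cases, does not match the stated question about the risk of having a CMD

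*Protocol article*

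**What the plan says.** **The question.** The Aim says that WP1 examines the risk of CMD. The WP1 objective asks: "Do people with different GBS access through time have different associated risks of having a CMD". The Design section describes the association of changes in GBS "on the risk of CMD (WP1) and SWB (WP2"). The Discussion gives the overarching aim as to "determine whether a positive change in access and exposure to GBS lowers the risk of CMD".

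**The primary outcome.** The section on the primary outcome for WP1 and 2 defines it as "Change in counts of CMD treatments for adults identified as CMD cases within the corresponding time periods", and the sentence goes on "for the 70% of adults in Wales for whom we have GP data records in SAIL (1.7M adults"). The case algorithm combines "an historical diagnosis and currently treated, with current diagnosis whether treated or untreated, to identify CMD cases". The count is built as follows: "For each adult, and for the time periods (quarters) identified as a CMD case, treatments will be counted per day and aggregated into quarterly counts".

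**The analysis.** The Analysis plan recognises two outcome types only, continuous (well-being) and counts (CMD treatments and GP event days), and states that "Poisson models will be used to analyse the longitudinal count data". Table 2 lists CMD as a count. The secondary WP1 outcome, GP event days, deliberately covers all GP activity and not only CMD-related activity.

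**The concern.** The risk of having a CMD in a population changes when people become cases or cease to be cases. A treatment count taken only where case status already holds describes something else: how intensively current cases are treated. Case status also arises after exposure and is partly defined by treatment, so restricting to case quarters conditions on something close to the outcome itself.

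The study is meant to inform planning and environmental policy. If GBS reduced onset or sped recovery without changing how remaining cases are treated, a case-only rate ratio would sit near 1 and could be reported as no effect on CMD risk, although risk had not been modelled. If mainly mild cases left case status, the mean count among those who remain could rise, and a benefit could look like harm.

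**Working it through.** The article gives no CMD incidence, recovery rate or treatment rate, and no planned figure to reproduce. Every rate below is an assumption. The calculations show direction and possible range, not the bias in this study.

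**1. Which outcome could carry the risk question?** Three kinds are listed: CMD treatment counts, GP event days and well-being scores. GP event days are all-cause, and well-being is not CMD. None is case status, onset or remission.

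**2. An effect on onset or recovery only.** Let i be quarterly incidence, r quarterly recovery and m the mean count in a case quarter. Long-run prevalence is p = i/(i + r). The mean count is p × m over all quarters (non-case quarters scored 0) and m over case quarters alone. Suppose GBS multiplies i by 0.8 and leaves m unchanged:

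| i | r | p before | p after | Ratio, all quarters | Ratio, case quarters |
|---|---|---|---|---|---|
| 0.01 | 0.05 | 0.01/0.06 = 0.167 | 0.008/0.058 = 0.138 | 0.828 | 1.00 |
| 0.01 | 0.10 | 0.01/0.11 = 0.091 | 0.008/0.108 = 0.074 | 0.815 | 1.00 |
| 0.02 | 0.10 | 0.02/0.12 = 0.167 | 0.016/0.116 = 0.138 | 0.828 | 1.00 |

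With factors of 0.9 and 0.7 the all-quarter ratios are 0.908 to 0.915 and 0.720 to 0.737; the case-quarter ratio stays at 1.00. Dividing r by the same factor gives the same ratios.

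**3. Selection through the treatment arm.** Suppose *currently treated* is judged within the quarter. A person who qualifies only through a historical diagnosis is then a case only with at least one treatment, so a zero cannot occur in that arm. Let counts be Poisson with mean μ, and let q be the share of quarters under a current diagnosis, kept whatever the count. The mean among kept quarters is f(μ) = μ / [q + (1 − q)(1 − e^(−μ))]. For a true treatment-rate ratio of 0.80, the observed ratio is f(0.8μ)/f(μ):

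| μ per quarter | q = 0 | q = 0.5 |
|---|---|---|
| 0.25 | 0.976 | 0.827 |
| 1 | 0.918 | 0.842 |
| 3 | 0.836 | 0.817 |
| 6 | 0.805 | 0.802 |

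For example, at μ = 1 and q = 0: f(0.8) = 0.8/0.551 = 1.453, f(1) = 1/0.632 = 1.582, ratio 0.918. The attenuation is strong only where treatment is sparse and few quarters carry a current diagnosis.

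**4. Mild cases leaving.** Take two equal groups of cases with mean counts 3 and 1, so a baseline mean of 2. If 20% of the mild group leave case status, the case-quarter mean is (0.4 × 1 + 0.5 × 3)/0.9 = 2.11, a ratio of 1.056. The all-quarter ratio is 1.9/2 = 0.95. With 10% to 30% leaving, and severe means of 3 or 6, the case-quarter ratio is 1.03 to 1.13 while the all-quarter ratio is 0.99 to 0.93.

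**5. Change against count.** The outcome sentence opens with a change in counts. The later sentence in the same section, the Analysis plan and Table 2 describe plain quarterly counts under a Poisson model. A difference can be negative and a Poisson variable cannot, so the two wordings do not agree.

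**The case against.** The strongest reply is that no sentence excludes non-case quarters. The outcome sentence itself names the 1.7 million adults with GP records, Participants describes the total registered adult population, and the three-level structure in the Analysis plan carries no restriction to cases. The wording could describe how a treatment comes to count as CMD treatment, with zeros elsewhere. On that reading the truncation in step 3 goes, and onset and recovery do move the count. This stands, and it limits the point. It does not remove it: the literal wording restricts to cases, the two readings estimate different quantities, and the zero-filled count still blends CMD risk with treatment intensity.

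A second reply is that the window for current treatment, the algorithm's details and the handling of non-case quarters may be in a fuller plan, and that Figure 4 is not shown. Their absence is not criticised here. The point is that the primary outcome and the list of outcome types, as stated, do not match the stated question.

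Three stronger readings are tempting and are not supported:

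- A reader might infer that the study cannot address CMD risk and discards every quarter in which people improve. Exclusion is not explicit, and even if it applies, people with a current diagnosis can stay in with a lower or zero count. Only quarters that no longer meet the definition would be lost.
- A reader might apply the Introduction's one in four to 1.7 million and conclude that about 425,000 adults inform the outcome. That is a UK background statement, not a case rate from this algorithm.
- A reader might infer that a quarter-to-quarter difference will be fitted as Poisson. Nothing specifies this; the quarterly differences described in the GBS accessibility and exposure dataset section are for exposure.

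**Conclusion.** The mismatch holds: the WP1 question concerns the risk of having a CMD, and the primary outcome as worded is a treatment count in adults and quarters already identified as cases, with no case-status, onset or remission outcome beside it. On the literal reading an effect on entering or leaving case status is not captured, and the analysis partly selects on the outcome through the treatment-dependent arm. On the zero-filled reading the count responds to risk, but not to risk alone.

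The size is unknown. The contrast between 0.815 to 0.828 over all quarters and 1.00 in case quarters rests on assumed incidence and recovery rates and on unchanged treatment among cases. The attenuation in step 3 further assumes a within-quarter treatment window and could be slight. The change-against-count conflict is one of wording.

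**What to change.** - For the risk question, model the algorithm's quarterly CMD case status (0/1) over all registered adult-quarters as a repeated binary outcome within the same three levels. Optionally split it into onset among non-cases and remission among cases.
- Keep the quarterly treatment count as a further outcome over all adult-quarters, and state that non-case quarters score 0.
- Interpret any count restricted to case quarters as treatment intensity, not CMD risk.
- Delete *Change in* from the outcome wording so that it agrees with the Poisson count in the Analysis plan and Table 2, and add the binary outcome to both.

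The cost is small. The algorithm already identifies case quarters, so no new data are needed. There is one extra model, and case status is a less graded outcome than a count. This answers the stated question whichever reading of the present wording was intended.
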